# Double blind, randomized, placebo controlled clinical trial for the treatment of diabetic foot ulcers, using a nitric oxide releasing patch: PATHON

**DOI:** 10.1186/1745-6215-8-26

**Published:** 2007-09-26

## Abstract

**Background:**

Diabetes Mellitus constitutes one of the most important public health problems due to its high prevalence and enormous social and economic consequences. Diabetic foot ulcers are one of the chronic complications of diabetes mellitus and constitute the most important cause of non-traumatic amputation of inferior limbs. It is estimated that 15% of the diabetic population will develop an ulcer sometime in their lives. Although novel therapies have been proposed, there is no effective treatment for this pathology. Naturally produced nitric oxide participates in the wound healing process by stimulating the synthesis of collagen, triggering the release of chemotactic cytokines, increasing blood vessels permeability, promoting angiogenic activity, stimulating the release of epidermical growth factors, and by interfering with the bacterial mitochondrial respiratory chain. Topically administered nitric oxide has demonstrated to be effective and safe for the treatment of chronic ulcers secondary to cutaneous leishmaniasis. However, due to their unstable nitric oxide release, the topical donors needed to be applied frequently, diminishing the adherence to the treatment. This difficulty has led to the development of a multilayer polymeric transdermal patch produced by electrospinning technique that guarantees a constant nitric oxide release. The main objective of this study is to evaluate the effectiveness and safety of this novel nitric oxide releasing wound dressing for the treatment of diabetic foot ulcers.

**Methods and design:**

A double-blind, placebo-controlled clinical trial, including 100 diabetic patients was designed. At the time of enrollment, a complete medical evaluation and laboratory tests will be performed, and those patients who meet the inclusion criteria randomly assigned to one of two groups. Over the course of 90 days group 1 will receive active patches and group 2 placebo patches. The patients will be seen by the research group at least every two weeks until the healing of the ulcer or the end of the treatment. During each visit the healing process of the ulcer, the patient's health status and the presence of adverse events will be assessed. Should the effectiveness of the patches be demonstrated an alternative treatment would then be available to patients.

**Trial registration:**

NCT00428727.

## Background

Diabetes Mellitus (DM) constitutes one of the most important public health problems with a worldwide impact due to its high prevalence and enormous social and economic consequences. It is believed that there are more than 135 million diabetics, and this number is expected to increase to 300 million in the next 25 years (30% in developed and 70% in developing countries) [1,2].

This epidemic is related to several factors like ethnicity, the longer life expectancy, and the epidemiological and nutritional transition in developing countries due to the urbanization process that brings about obesity and sedentarism [3,4]. In Colombia, the 2002 basic health indicators showed a 2% prevalence of DM. However, it is believed that these numbers are underestimated [5]. Diabetic Foot Ulcers (DFU) are one of the chronic consequences of DM which constitute the most important cause of non-traumatic amputation of the Inferior Limbs (IL), and are associated with high human, social and economic costs [6-11]. It is estimated that approximately 15% of the diabetic population will develop a DFU some time in their life [12-16].

DFU is a consequence of two of the most frequent chronic complications of DM: Peripheral neuropathy and vascular insufficiency [12]. The combination of these factors in association with mechanic extrinsic and intrinsic aggressions, like feet bone deformations, triggers the ulcer formation. This polyfactorial etiopathology explains the multidisciplinary approach required for this disease [17-19].

The early detection of risk factors for DFU may prevent their appearance [20-28]. This is why the monitoring of neuropathic, vascular and muscle-skeletal functions [29], the reinforcement of self care [30], the control of glycemic levels and the prevention of traumatic foot lesions [21,23,24,31], have a positive impact on the prevention of this pathology.

The wound healing process involves the interaction of multiple cellular groups, extra cellular matrix molecules and growth factors [32], and is affected by vascular insufficiency, the severity of the lesion and the presence of infection [18,24].

Immune and wound healing mechanism dysfunctions have been described in diabetic patients [33]. This alteration of the immune response is characterized by a decrease in the adherence of leukocytes to the capillary endothelium, chemotaxis damage and a reduction in the ability of polymorphonuclear cells to phagocyte and destroy bacteria due to a minor production of Nitric Oxide (NO) [34,35]. Diabetic patients also show a diminution in fibroblasts activity provoked by the unavailability of glucose for the aerobic metabolism, leading to inadequate fibrous collagen tissue proliferation [36]. The imbalance in these processes has been described as the main cause for the appearance and persistence of DFU [37].

Alternative therapies for DFU have been proposed, such as tissue engineering [38], growth factors [39], hyperbaric oxygen therapy [40,41] and ketanserine [42,43]. Various types of products have also been used to keep the wound dry and covered (hydrogels, hydrocolloids, alginates and foams) [44], however, there is no effective treatment for this pathology [45,46].

In normal conditions, NO is continuously produced [47] and is tightly linked to many physiological processes, among which wound healing. It has been described that NO stimulates collagen synthesis [48], triggers the release of chemotactic cytokines [49], and has an important microbicidal effect by interfering with the enzymatic processes of the bacterial mitochondrial respiratory chain [50]. It also increases blood vessels permeability [51-54], promotes angiogenic activity, and stimulates the release of epidermical growth factors [37,55].

Various studies, performed in murine models, have demonstrated the role of NO in the healing process. The levels of the final metabolic products from NO (nitrite and nitrate) rise during the first two days more than subsequently in the liquid recovered from the sponges previously placed in the subcutaneous tissue of healthy subjects' wounds [56], increase that is not observed in diabetic subjects [54], suggesting an impairment in the cutaneous production of NO in diabetic individuals. The topical use of NO accelerates the wound healing process of excisional wounds [54,57] while NO inhibitors increase the healing time of these lesions [48,58]. The use of colloid NO donors in diabetic subjects shows an adequate granulation and closing of wounds [59,60].

Our experience in the treatment of cutaneous leishmaniasis with s-nitroso-N-acetilpenicilamine (SNAP), a NO donor, shows a beneficial effect without adverse events [61]. Moreover, a clinical trial is being conducted to study the effectiveness of a controlled NO releasing patch in the treatment of cutaneous leishmaniasis [62]. Currently, there are no studies using topical NO donors in humans with diabetic ulcers. Though the use of NO donors in healthy volunteers has shown an adequate NO diffusion rate to dermis, and an increase in the microcapillar blood flow [63], this method has demonstrated not to be effective due to the short half life and release span of NO [61].

This difficulty in controlling the stability and release of NO has led to the development of a new NO releasing patch (NOP). This device, produced by the electrospinning technique [64], is a multilayer polymeric transdermal patch in which the principal components are stabilized and encapsulated in nanofibers which guarantees a constant NO release upon its hydration.

Since it is well known that the system generates NO almost immediately, nitrite ions are bound to an ionic exchange resin (DOWEX^®^) in order to stabilize them, allowing a constant release of 3.5 μmol of NO during 12 hours or more depending upon the dosage [64]. This device has been tested by our group for the treatment of cutaneous leishmaniasis obtaining encouraging results in the healing process with no report of serious adverse events [61]. Since there is no specific effective treatment for DFU our group proposes to investigate the topical use of NOP, elaborated by the electrospinning technique, for the treatment of DFU.

### Objectives

#### General Objective

To evaluate the effectiveness and safety of NOP for the treatment of DFU.

#### Specific Objectives

1. To evaluate the healing process of DFU using a NOP compared with placebo.

2. To assess the healing process of infected DFU using a NOP compared with placebo.

3. To identify adverse events associated with the application of NOP.

## Methods and design

Double blind, randomized, placebo controlled clinical trial.

### Sample size

The sample was calculated according to the arccosine formula considering a power of 80% and a type I error of 0.05. Assigning a successful rate of 30% in the control group and 60% in the active group, 95 participants will be needed. After adjusting for a loss rate of 5%, the total number of patients that must be recruited is 100 (50 patients per group).

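### The stated formula and inputs give 84 patients, not 95; at 95 the named formula gives about 85% power rather than 80%, a conservative mismatch to be restated

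*Protocol article*

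**What the plan says.** The Sample size section of the protocol article sets out a complete calculation. The method, power and error rate come first: "The sample was calculated according to the arccosine formula considering a power of 80% and a type I error of 0.05". The effect follows: "Assigning a successful rate of 30% in the control group and 60% in the active group". The result is given as "60% in the active group, 95 participants will be needed". After an allowance of 5% for losses, "the total number of patients that must be recruited is 100 (50 patients per group").

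The section does not say whether the 0.05 is one-sided or two-sided, and it mentions no continuity correction. The Statistical analysis section says that categorical variables will be compared by a chi-square test or Fisher's exact test, and it plans two interim analyses, at 35% and 70% of the sample. The Sample size section does not mention them.

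**The concern.** The section names a formula, gives every numerical input the formula needs, and gives an output. A reader should be able to put the inputs in and get the output, but cannot: the formula gives a total well below 95. At least one of three statements (the formula, the power or the size) is therefore not what was actually used.

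The practical stake is modest but real. A reader cannot tell whether the extra patients reflect a slip, a different power target, an undisclosed correction or a different test. These imply different power for the trial as it will be run: about 85% if the plain formula is taken at face value, about 79% if a continuity-corrected approximation was intended. Anyone who relies on this paragraph later, for example to judge whether losses above 5% are tolerable, needs to know which applies.

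**Working it through.** **Inputs, all from the Sample size section:** control success rate 0.30; active success rate 0.60; type I error 0.05; power 80%; equal groups; losses 5%. Sidedness is not stated, so both were tried.

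**Effect size.** On the angular scale, h = 2·arcsin√0.60 − 2·arcsin√0.30 = 1.7722 − 1.1593 = 0.6129. The arccosine version gives the same absolute difference, so the choice of name does not matter.

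**Loss adjustment.** 95 / 0.95 = 100. This step reproduces.

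**Sample size by the named formula.** n per group = 2(z_α + z_β)² / h², with h² = 0.3756.

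- Two-sided 0.05, 80% power: 2(1.960 + 0.8416)² / 0.3756 = 2 × 7.849 / 0.3756 = 41.8, so 42 per group and 84 in total (89 after 5% losses).
- One-sided 0.05, 80% power: 2(1.645 + 0.8416)² / 0.3756 = 32.9, so 33 per group and 66 in total.

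Neither gives 95. Against the two-sided result the difference is 95 − 84 = 11 patients, and 11/84 = 13%.

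**Power at the stated size.** Power = Φ(h√(n/2) − 1.960), two-sided.

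- 95 evaluable (47.5 per group): Φ(2.987 − 1.960) = Φ(1.027) = 84.8%.
- 100 evaluable (50 per group): Φ(3.064 − 1.960) = Φ(1.104) = 86.5%.

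**Which other calculations land near 95?**

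| Calculation (two-sided 0.05) | Total needed | Power at 95 |
|---|---|---|
| Angular formula, 80% power, as stated | 84 | 84.8% |
| Angular formula, 85% power | 95.6 unrounded, 96 in whole groups | 84.8% |
| Angular formula with continuity correction, 80% power | 96.5 unrounded, 98 in whole groups | about 79% |
| Pooled normal formula with continuity correction, 80% power | 96.8 unrounded, 98 in whole groups | about 79% |
| Fisher's exact test, 80% power | 96 (80.0% at 48+48) | about 82% (47+48) |

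The continuity correction is n_c = (n/4)·[1 + √(1 + 4/(n·d))]², with n = 41.8 and d = 0.30, which gives 48.2 per group.

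Fisher power was found by enumerating all outcomes under 30% and 60%. With 47 control and 48 active patients it is 81.9%; with the split reversed it is 82.5%. At 47+47 it is 78.6%, and at 42+42 only 76.4%. The same enumeration for the uncorrected chi-square test gives 85.4% at 47 control and 48 active.

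Several calculations come within one to three patients of 95. None of them gives exactly 95, and none is the calculation the section describes.

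**The case against.** The strongest reply is that nothing harmful has happened. Power of 80% is a planning input, and enrolling more than the minimum does not make it false. At 95 the target is met under the named formula (84.8%), under the chi-square test (85.4%) and under Fisher's exact test (about 82%). A condensed journal article might well leave out a continuity correction, and with one the stated 95 has about 79% power, which is 80% to within rounding. An omitted variant is then as plausible an explanation as an error.

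Most of this stands. It disposes of the reading that a reader might infer from a figure that fails to reproduce, namely that the trial is underpowered or that its 80% target is missed. The documents do not support that: the discrepancy runs in the safe direction under the stated formula, and both tests named in the Statistical analysis section keep at least 80% at 47+48.

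It does not remove the mismatch. The section is not silent on method: it names one formula and gives all its numbers, and they disagree. That 95 might come from an unstated correction is a conjecture, and the corrected formula does not give 95 either (96.5, or 98 in whole groups).

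Two further inferences should also be resisted. One is that 84 would be enough. That holds only for the uncorrected approximation; under Fisher's exact test, 42+42 has 76.4% power. The other is that the surplus was meant to cover the interim analyses. The article names no stopping boundary and does not link the sample size to those looks.

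**Conclusion.** The point holds as a reporting error in a key planning figure. The named formula with the stated inputs gives 84 (two-sided) or 66 (one-sided), not 95, and 95 evaluable patients have about 85% power by that formula, not 80%. The gap is 11 patients, or 13% of 84, and about 5 percentage points of power. It is conservative, and it is no evidence that the trial is too small.

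The figures of 84 and 85% assume a two-sided test, which the section does not state, with equal groups and no correction. The one-sided alternative moves further from 95, so the mismatch does not depend on that assumption. The cause of the discrepancy cannot be settled from the article.

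**What to change.** Keep recruitment at 100, 50 per group, and restate the Sample size paragraph so that formula, sidedness, power and size agree. Which of two forms applies depends on what was done:

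- If the uncorrected angular formula is kept: *With 95 evaluable patients, success rates of 30% v 60% and two-sided 0.05, power is about 85% by the uncorrected arcsine formula (about 82% by Fisher's exact test).*
- If a continuity correction or an exact test was used: name it, and give the size and power that it yields.

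If 84 is mentioned at all, say that it applies only to the uncorrected approximation. Do not bring an interim boundary into this paragraph, since the article does not specify one.

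The cost is one paragraph of wording. Enrolment and analysis do not change.

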### Population

The population will be composed of patients with a confirmed diagnosis of DM type 1 or 2 who present DFU, meet the inclusion criteria and don't present any criterion that could exclude them.

### Inclusion criteria

1. Men and women 18 years or older.

2. Capacity of attending the visits at the research site.

3. Confirmed diagnosis of DM type 1 or 2 according to the guidelines from the American Diabetes Association (ADA).

4. Presence of 1 or more DFU, less than 15 cm in its biggest diameter, with a Texas University score ≤ 2.

5. Pharmacological treatment for glycemic control.

6. Willingness to participate in the study and to sign the informed consent form.

### Exclusion criteria

1. Unconfirmed DM diagnosis.

2. Any pathology that, based on the judgment of the researcher, could alter the course of DFU (neoplasias, immunological disorders, etc).

3. Renal insufficiency requiring dialysis treatment.

4. DFU with aTexas score >2.

5. Infected DFU with clinical or paraclinical findings suggesting osteomielytis.

6. Critical ischemia of IL diagnosed by Doppler ultrasound and defined by ankle/arm index < 0.5.

7. Clinical findings suggesting complicated venous insufficiency of IL.

8. Distal necrosis of the limb with the ulcer.

9. Pregnant or breastfeeding women.

10. Mentally or neurologically disabled patients that are considered not fit to approve their participation in the study.

11. Refusal to give informed consent.

### Study development

See table 1.

**Table 1 T1:** Schedule of activities

	**Follow-up visits**							
**PROTOCOL ACTIVITIES**	**Screening Visit**	**Initial Visit**	**Visit 1**	**Visit 2**	**Visit 3**	**Visit 4**	**Visit 5**	**Final Visit**
**SCHEDULE OF VISITS**		0	15 ± 5	30 ± 5	45 ± 5	60 ± 5	75 ± 5	90 ± 5
Clinical History	X	X	X	X	X	X	X	X
Physical Examination	X	X	X	X	X	X	X	X
Inclusion/Exclusion criteria	X							
Informed Consent	X							
Clinical assessment of vascular compromise	X	X	X	X	X	X	X	X
Clinical assessment of neuropathic compromise		X						X
Laboratory tests		X						X
Ankle/arm index	X							
Randomization		X						
Treatment administration		X	X	X	X	X	X	
Clinical assessment of the lesion	X	X	X	X	X	X	X	X
Measurement of ulcers	X	X	X	X	X	X	X	X
Photographic registration		X	X	X	X	X	X	X
Education of patients	X	X	X	X	X	X	X	X
Documentation of adverse events	X	X	X	X	X	X	X	X
Recording of concomitant medications	X	X	X	X	X	X	X	X

### Logistic phase

This phase will be managed by the physician in charge of the study and a professional nurse and will include the following activities.

1. Acquisition of the materials required for the development of the project.

2. Elaboration of flyers, promotional and educative material, procedures manual and Case Report Format (CRF).

4. Training of personnel that will participate in the study.

5. Treatment randomization

The treatment randomization will be realized by the epidemiologist of the Fundación Cardiovascular de Colombia (FCV). This randomization will be done in blocks in order to avoid long sequences of patients assigned to the same group and to reduce when possible, some of the bias inherent to the simple randomization process. Additionally, this randomization in blocks will facilitate the execution of interim analyses.

### Recruitment phase

Patients will attend the screening visit at the FCV or at the offices of the physicians involved in the study.

### Screening visit

During this visit a complete medical check-up, based on universally accepted techniques, will evaluate risk factors, DM complications, vascular and neuropathic compromise, medications and other therapies used for the treatment of DFU. The ankle/arm index will be obtained to rule out the presence of critical IL ischemia. The inclusion/exclusion criteria will be applied and the selected candidates informed about the study after which they will sign an informed consent form. A blood sample will be withdrawn to determine the percentage of glycosilated hemoglobin (HbA1c), the levels of creatinine and fasting glucose, the hemogram, and the lipid profile.

The laboratory of the Research Institute of FCV and the laboratories of every other center will be in charge of the processing of blood samples. All the tests will be elaborated using standard techniques.

1. Glycosilated hemoglobin: Chromatography.

2. Creatinine: Spectrophotometry.

3. Hemogram: Manual method.

4. Lipid profile: Spectrophotometry.

5. Fasting glucose: Spectrophotometry.

### Initial visit

The selected patients will be scheduled for the initial visit. In this visit the patients will be randomly assigned to one of the two groups. Group 1 will receive NOP and Group 2 placebo patches. A complete medical evaluation will be performed, the ulcers measured, and their pictures taken. Neuropathy will be assessed using the modified validated neuropathic impairment score (NDS) [65]. Before taking the pictures, a graduated ruler will be placed next to the ulcers with a sticker marked with the identification code of the participant and the date of the visit. The first patch (active or placebo) will be applied on the lesion. All the information obtained will be registered in the CRFs. The treatment previously prescribed for DM or other concomitant pathologies, and the medical, surgical or orthopedic therapies for DFU will be continued with the exception of topical treatment. The researchers will follow the guidelines of the International Diabetic Foot Consensus (CIPD). The patient and his/her family will receive information regarding the treatment of DFU, the correct technique for the daily application of the patches and the identification and notification of adverse events.

### Follow-up visits

The treatment will last 90 days. During this period, the patients will be seen by the research group at least every two weeks until the healing of the ulcer or the end of the treatment. The frequency of the visits will vary depending on the clinical evolution of the patients. During each visit the healing process of the ulcer, the patient's health status and the presence of adverse events will be assessed. The patch will be applied and the evolution of the ulcers photographically registered. The maximum and minimum diameters of the ulcer will be measured using a graduated ruler and then registered in the CRF. The technique for the application of the patches, the identification of adverse events and the importance of reporting them, will be emphasized.

### Final visit

The final visit will take place at the end of the treatment or before in case of complete healing of the ulcer. A thorough medical evaluation, including laboratory tests will be performed along with the assessment of vascular and neuropathic compromise. The presence of adverse events will also be evaluated. The evolution of the ulcers will be documented by measuring their maximum and minimum diameters and by photographing them.

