### Endpoints

At the end of the treatment the following endpoints will be evaluated:

1. Ulcer reduction percentage.

2. Complete cure of the infection that was present before the treatment.

3. Infection of the ulcers during the treatment.

4. Presence of adverse events related to the application of the patches.

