### Evaluation and management of adverse events

During the visits the patients will be asked about adverse events. Each adverse event will be classified by the physician as serious or non-serious. A serious adverse event should meet one or more of the following criteria:

1. Death

2. Life-threatening

3. Hospitalization or prolongation of existing hospitalization

4. Persistent or significant disability/incapacity

The presence of a serious adverse event that puts the patient's life at risk and/or requires immediate medical or surgical procedure will call for the discontinuation of the treatment and the initiation of the pertinent medical management. The investigator will notify the Adverse Event Committee (AEC) of the FCV of any serious adverse event within 24 hours of learning about it.

A non-serious adverse event will be classified as follows:

1. Mild: The patient is aware of his/her symptoms and/or signs, but those are tolerable. Medical intervention or specific treatment is not required.

2. Moderate: The patients present troubles that interfere with his/her daily activities. Medical intervention or specific treatment is required.

3. Severe: The patient is unable to work or to attend his/her daily activities. Medical intervention or specific treatment is required.

The possible relationship between the adverse events and the tested medication will be classified by the investigator on the basis of his/her clinical judgment and the following definitions:

1. Definitely related: Event can be fully explained by the administration of the tested medication.

2. Probably related: Event is most likely to be explained by the administration of the tested medication rather than other medications or by the patient's clinical state.

3. Possibly related: Event may be explained by the administration of the tested medication or other medications or by the patient's clinical state.

4. Not related: Event is most likely to be explained by the patient's clinical state or by the use of other medications, rather than the tested one.

All the events will be reported to the AEC that, depending on its criteria, will decide the continuity of the patient in the study and therefore the breaking of the code. Although the project has been designed to minimize the inherent risks, any adverse event related to the study medication will be carefully evaluated by the AEC and the costs generated by the required treatment covered by the study.

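### Scheduled follow-up ends when the ulcer heals, so an early closure is never rechecked and early healers have no planned assessment up to day 90

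*Protocol article*

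**What the plan says.** Three parts of the protocol article together set how long a patient is observed.

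- **Follow-up visits.** "The treatment will last 90 days", but patients are seen "at least every two weeks until the healing of the ulcer or the end of the treatment".
- **Final visit.** "The final visit will take place at the end of the treatment or before in case of complete healing of the ulcer". Table 1 places this visit at day 90 ± 5 and schedules nothing after it.
- **Evaluation and management of adverse events.** "During the visits the patients will be asked about adverse events", so planned questioning about safety ends with the visits.

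The Endpoints section opens with "At the end of the treatment the following endpoints will be evaluated". It lists percentage reduction of the ulcer, cure of an infection present at the start, new ulcer infection during treatment, and "Presence of adverse events related to the application of the patches". The Statistical analysis section compares categorical variables by chi-square or Fisher's exact test. No section shown schedules a check that a closure has lasted, or any contact after healing.

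**The concern.** How long a patient is observed depends on the outcome that the patch is meant to change. This has two consequences.

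**Efficacy.** A patient whose ulcer closes at day 30 leaves with 100% reduction, from one observation. A patient whose ulcer stays open is measured at about day 90 and can worsen until then. If the first ulcer re-opens at day 60, the recorded result is still 100%. The rule works in one direction only, and it applies most often in the arm with more early closures.

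**Safety.** Safety is part of the general objective, and the two interim analyses also compare it. Delayed or general adverse events, and infection of an ulcer that re-opens, are not scheduled to be looked for in early healers. A plain proportion then compares arms that were watched for different lengths of time. Data not collected before day 90 cannot be recovered by analysis.

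**Working it through.** **Inputs from the documents.** Success rates 30% (control) and 60% (active), and 50 patients per group (Sample size); 90 days of treatment (Follow-up visits); visits 15 days apart (Table 1).

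**Assumption.** The document does not define success. Here it is read as complete healing by day 90.

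**The plan's own figure.** With h = 2·asin(√0.6) − 2·asin(√0.3) = 0.613, two-sided 0.05 and 80% power, the arcsine form gives 2(1.960 + 0.842)²/0.613² = 41.8 per group, or 84 in total. With a continuity correction it gives 48.2 per group, about 97 in total and close to the stated 95. Then 95/0.95 = 100. The sample size is not in dispute.

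**Step 1: expected healers.** 0.30 × 50 = 15 on control and 0.60 × 50 = 30 on active. These patients can leave before day 90.

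**Step 2: mean days observed.** At a constant healing rate λ = −ln(1 − p)/90, the mean of the earlier of healing and day 90 is p/λ.

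- Control: 0.30 × 90/0.3567 = 75.7 days
- Active: 0.60 × 90/0.9163 = 58.9 days
- Ratio: 58.9/75.7 = 0.78, about 22% less on active

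**Step 3: other healing-time assumptions.**

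| Assumption | Control (days) | Active (days) | Ratio |
|---|---|---|---|
| Constant rate | 75.7 | 58.9 | 0.78 |
| Constant rate, healing detected at 15-day visits | 78.0 | 63.5 | 0.82 |
| Healing times uniform over 90 days | 76.5 | 63.0 | 0.82 |
| Healers close at day 30 on average | 72.0 | 54.0 | 0.75 |
| Healers close at day 75 on average | 85.5 | 81.0 | 0.95 |

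The last two rows use 90(1 − p) + m·p, with m the mean healing day in both arms. If both arms heal alike, the ratio is 1.00 and nothing is distorted.

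**Step 4: effect on event proportions.** The document gives no event rate, so this step is illustrative. Take the same event rate g in both arms. The proportion recorded before healing or day 90 is g/(g + λ) × (1 − exp(−90(g + λ))).

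- 90-day risk 10%: 8.4% control, 6.6% active
- 90-day risk 20%: 16.9% and 13.3%
- 90-day risk 30%: 25.5% and 20.2%
- 90-day risk 40%: 34.2% and 27.2%

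The ratio stays at 0.78 to 0.80. What the gap means depends on the risk after closure:

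- If the event rate continues unchanged after closure, full follow-up at 30% risk would show 30% in both arms. The gap of 25.5 − 20.2 = 5.3 points is then an artefact.
- If the risk falls to zero at closure, full follow-up would show the same 25.5% and 20.2%. The gap is then a true consequence of healing.

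**Step 5: effect on closure.** If the same share r of closures re-opens in each arm and stays open to day 90, the difference in ulcers closed at day 90 falls from 30 points to 30(1 − r) points. The documents give no value for r.

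**The case against.** The strongest objection concerns the endpoints actually listed: infection of the ulcer during treatment, and events related to applying the patch. Once a patient's only ulcer has closed, no open ulcer can be infected and no patch is in use. Fewer such events in a faster-healing arm are then largely a real benefit. This stands. It is why the 5.3-point gap cannot be presented as a false benefit.

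Three further objections also hold.

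- **Precision.** With 50 per arm, the standard error of 25.5% against 20.2% is √(0.255 × 0.745/50 + 0.202 × 0.798/50), about 8.4 points. If the active patch raised the event rate by 30%, full follow-up would show 30% against 37.1%, with only about 11% power. A reader might infer that the stopping rule is what hides a harm, but trial size limits detection more.
- **Analysis method.** Rates per patient-time are commonly left to the analysis plan, so their absence here is not itself a fault.
- **Unscheduled reports.** A reader might infer that re-opening would never be seen. Patients and families are taught to recognise and report adverse events, and an unscheduled return is not excluded. The document supports only that no such assessment is scheduled.

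A reader might also infer that patients withdrawn after an adverse event have no day-90 outcome. The committee "will decide the continuity of the patient in the study and therefore the breaking of the code", but the text does not say that assessment of such patients stops.

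None of this answers the efficacy point, or the missing scheduled look for re-opening and for delayed or general events.

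**Conclusion.** The point holds in a limited form. As written, one observed closure fixes the outcome and ends scheduled observation, and no section shown offsets this. On the plan's own rates the active arm would be watched for about 0.78 of the control arm's time, with a range of 0.75 to 0.95. This rests on reading 30% and 60% as healing by day 90 and on assumed healing times. It also requires the arms to heal at different rates, as the design expects.

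The size of any bias is unknown, both for adverse events and infections and for ulcer reduction. It would matter most for delayed or general adverse events, infection after re-opening, and closures that do not last. The documents do not support a stated false safety benefit or a claim that harm is concealed. This is a cheap improvement to make in the protocol; it does not invalidate the design.

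**What to change.** 1. Keep the day 90 ± 5 visit of Table 1 for every randomised patient, including those healed early or off the patch.
2. Evaluate ulcer reduction and closure at that visit. Record the date of first closure and of any re-opening. Since patients may enter with more than one ulcer, state which closure counts as healing.
3. Report adverse events and infections per patient-day on patch, using dates already recorded, and over the full 90 days, beside the proportions. The two views separate risk while on the patch from the total effect, which includes the benefit of healing.
4. Reconcile the adverse-event wording on stopping treatment, leaving the study and breaking the code, so that it is clear which of these is meant and whether outcome assessment continues.

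Items 1 to 3 change observation and analysis only, not treatment. The cost is one already-scheduled visit per early healer, about 15 + 30 = 45 patients if the planning rates hold, and a possibly slightly lower healing rate once re-opened ulcers no longer count as closed. A single visit at day 90 will not date re-openings exactly or match two-weekly detection of adverse events, but it gives both arms the same end point.
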